### 8.2.3 Reporting Responsibilities

All SAEs, SARs and SUSARs (excepting those specified in this protocol as not requiring reporting) will be reported immediately (and certainly no later than 24hrs) by the Investigator to the KHP-CTO and CI for review in accordance with the current Pharmacovigilance Policy. The KHP-CTO will report SUSARs to the regulatory authorities (MHRA, competent authorities of other EEA (European Economic Area) states in which the trial is taking place. The Chief Investigator will report to the relevant ethics committee. Reporting timelines are as follows:

- ☐ SUSARs which are fatal or life-threatening must be reported not later than 7 days after the sponsor is first aware of the reaction. Any additional relevant information must be reported within a further 8 days.
- ☐ SUSARs that are not fatal or life-threatening must be reported within 15 days of the sponsor first becoming
- ☐ aware of the reaction.

The Chief Investigator and KHP-CTO (on behalf of the co-sponsors), will submit a Development Safety Update Report (DSUR) relating to this trial IMP, to the MHRA and REC annually.

### 8.2.4 Treatment stopping rules

The trial may be prematurely discontinued by the Sponsor, Chief Investigator or Regulatory Authority on the basis of new safety information or for other reasons given by the DMEC/TSC regulatory authority or ethics committee concerned. If the trial is prematurely discontinued, active participants will be informed and no further participant data will be collected. The Competent Authority and Research Ethics Committee will be informed within 15 days of the early termination of the trial.

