### **2.4 Endpoints**

#### **2.4.1 Primary Endpoint**

- i) Delivery < 37 completed weeks' gestation (powered).

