### **3.3 Study visit 1: Randomisation and intervention (14+0-23+6 weeks' gestation)**

At time of recruitment women will be randomly assigned (1:1:1) to cerclage, progesterone or pessary. Randomisation will be carried out online via the Medscinet web portal ([www.medscinet.net](http://www.medscinet.net)). Users will be assigned a personal identifier number. Due

[figure not shown]

to the nature of the interventions, the study is not blinded to the clinician or patient. Recruiters and trial coordinators will not have access to the randomisation sequence. Women will be informed at time of recruitment to which arm they have been randomised. A 'minimisation' procedure, using a computer-based algorithm, will be used to avoid chance imbalances in important stratification variables. Stratification variables will be a) gestation, b) BMI <30 or >30 kg/m^2 c) risk factor (previous premature delivery <24 weeks & previous cervical surgery). Women will not know what treatment they will be allocated prior to recruitment. Medscinet will write the randomisation program and hold the allocation code. Contact information will be obtained from the patient. Demographic measures will be entered into the central trial database. Following randomisation, the obstetrician will then arrange for the intervention to be performed as the randomisation indicates. There is no 'emergency code break' procedure as the trial is an open label RCT.

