### 3.7 Withdrawal from study

Participation in the study is voluntary. A patient has the right to discontinue drug/pessary or completely withdraw from the study at any time for any reason. The Investigator has the right to discontinue a patient taking drug/pessary at any time if it is deemed to be in the patient's best interest. If a participant elects to withdraw from the study no further samples will be collected. Identifiable data or tissue already collected with consent would be retained and used in the study if the women consents for it to be so. Consent would be sought to collect use the participant's delivery details (if delivery has not yet occurred). If a participant who has given informed consent loses capacity to consent, the participant would be withdrawn from the study. Identifiable data or tissue already collected with consent would be retained and used in the study. No further data or tissue would be collected or any other research procedures carried out on or in relation to the participant. If the participant is withdrawn due to a serious adverse event, the Principal Investigator will arrange for follow-up visits or telephone calls until the event has resolved or stabilised. However as the participants are pregnant women data will be collected routinely to outcome (i.e. delivery) and used in the analysis unless the consent to collect the outcome is specifically refused by the participant.

If an eligible patient is excluded or refuses to participate, the reasons for this will be documented where possible for input into trial metrics.

[figure not shown]

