## 5 Sample size, power and statistical analysis

Our previous experience (captured by a robust database of outcome data from >2000 women attending our prematurity clinic) indicates that approximately 50% of women with short cervixes (<25 mm) treated with cerclage deliver early <37 weeks. From existing published evidence, we have good reason to believe that cerclage, vaginal progesterone and silicone pessary are all of approximately equal efficacy and reduce the rate of prematurity in women from 75% (untreated) to around 50% [6,8,9,15]. We therefore determine to confirm this by a 3-arm equivalence study. Equivalence is defined as agreement to within 20% (e.g. 40% to 60%). Following Jones *et al* (1996), we allow for differences in both directions in calculating the power. Complete data on 170 women per arm (510 in all) will give us 90% power to detect difference clinically important differences of 20% or more in either direction. To allow for dropouts, we aim to recruit 540 women in total.

Analysis will be according to intention to treat. The main outcome is delivery before 37 weeks'. Results will be presented as both odds ratios and risk differences, leading to number needed to treat (NNT) if appropriate, according to CONSORT guidelines. Given that high risk women with a history of invasive cervical surgery, and those with incidental findings of a short cervix may have a different pathophysiology to those women with a history of preterm birth, sub-group analysis will be performed according to risk factor. As we are powering for equivalence in the maternal outcome, it is not anticipated that the neonatal outcomes will be different however we will collect data on composite neonatal end point (not specifically powered for equivalence).

For biomarker analysis, results will be analysed at each time point in a cross sectional analysis, and on a case-control basis. We will express the overall usefulness of each marker for prediction of the primary outcome as a ROC area (Receiver Operating Characteristic), with 95% confidence interval and p-value. We will describe the performance of the most useful markers in terms of sensitivity, specificity and related measures for selected cut-points. We will use logistic regression in order to identify possible useful combinations of markers; where possible, we will use the repeated measurements to describe the change in test performance with gestation.

[figure not shown]

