## **6 Collection of outcome data**

Women will be followed up until postnatal discharge. Neonates will be followed up to discharge or 28 days (whichever is sooner). Prompts on the database will alert the research midwife/assistant when each trial participant reaches her delivery date. Birth registers and in-patient records will also be used to track hospital admissions and pregnancy outcomes. Outcome data (medical and economic) will be collected by review of obstetric handheld/electronic notes. The primary and secondary outcome data will be collected after discharge from neonatal care.

Measurement of outcome (medical and economic): will be collected via electronic patient records, and/or hand-held patient notes. If information is not available, e.g. if the delivery occurred elsewhere, the patient, patient's GP or other hospital will be contacted. Gestational age will be calculated using ultrasound estimated date of delivery predicted at the 12-15 week scan, or last menstrual delivery if miscarriage occurs prior to dating scan.

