**Serious adverse Event (SAE), Serious Adverse Reaction (SAR) or Unexpected Serious Adverse Reaction (SUSAR):**

Any adverse event, adverse reaction or unexpected adverse reaction, respectively, that

- Results in death
- Is life-threatening;
- Required hospitalisation or prolongation of existing hospitalisation;
- Results in persistent or significant disability or incapacity - Consists of a congenital anomaly or birth defect.
- Is otherwise considered medically significant by the investigator.

All AEs and SAEs must be recorded from the time a participant is randomized to treatment until 30 days after stopping taking study drug and until pregnancy outcome (28 days after delivery). The Investigator should ask about the occurrence of AEs/SAEs at every visit during the study. Open-ended and non-leading verbal questioning of the participant should be used to enquire about AE/SAE occurrence. Participants should also be asked if they have been admitted to hospital, had any accidents, used any new medicines or changed concomitant medication regimens. If there is any doubt as to whether a clinical observation is an AE/SAE, the event should be recorded. Hospitalisations for treatment planned prior to randomisation and hospitalisation for elective treatment of a pre-existing condition will not be considered as an SAE. Complications occurring during such hospitalisation will be AE/SAEs.

**Important Medical Events (IME):** Events that may not be immediately life-threatening or result in death or hospitalisation but may jeopardise the patient or may require intervention to prevent one of the other outcomes listed in the definition above should also be considered serious.

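### Section 8.2.4 ends all data collection if the trial stops early, so nearly all women still pregnant would lose their primary outcome and safety follow-up

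*Protocol*

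**What the plan says.** Section 8.2.4 sets out who may end the trial: "The trial may be prematurely discontinued by the Sponsor, Chief Investigator or Regulatory Authority on the basis of new safety information", or for other reasons. In that event, "active participants will be informed and no further participant data will be collected". There is no exception for delivery or safety data, and no other section overrides the sentence for a trial-level stop.

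Elsewhere the protocol treats follow-up differently:

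- Section 3.7 (Withdrawal from study) says of women who withdraw individually that "data will be collected routinely to outcome (i.e. delivery) and used in the analysis", unless the woman specifically refuses.
- Section 8.2.1 opens its safety window with "All AEs and SAEs must be recorded from the time a participant is randomized" and closes it 30 days after the study drug ends and 28 days after delivery.
- Section 6 takes outcomes from birth registers and patient notes. Section 3.6 says that the 28-day note review needs no contact with the woman.
- Section 5 specifies intention to treat.

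**The concern.** The primary endpoint is delivery before 37 weeks. Women are randomised at 14+0 to 23+6 weeks, so about 13 to 23 weeks pass before 37+0 is reached. At any stop during recruitment, a sizeable group has been randomised and treated but has not delivered. Section 8.2.4 discards their outcomes, although ending recruitment or treatment gives no reason to stop reading routine records.

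Three things are at stake:

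- **Precision.** A stopped trial is already small, and the rule makes it smaller.
- **Safety.** The first ground named for stopping is new safety information. The women most recently exposed are then the ones who go unobserved.
- **The crude rate.** Preterm births resolve sooner than term births, so women delivered by a cut-off date include too many of them.

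An analysis plan cannot repair this, because it cannot recover data that the protocol says will not be collected.

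**Working it through.** **Inputs from the protocol.** 540 women over 36 months (section 3.7, Expected duration), i.e. 540/36 = 15 per month, or 15/4.348 = 3.45 per week. Entry at 14+0 to 23+6 weeks (section 3.3). Preterm rate 50%: "approximately 50% of women with short cervixes (<25 mm) treated with cerclage deliver early <37 weeks" (section 5). 510 complete cases needed, so the loss allowance is 540 − 510 = 30 women, or 30/540 = 5.6%. Equivalence margin 20 points.

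**Assumptions not in the protocol.** Uniform accrual; entry gestation uniform over the ranges below; mean gestation of preterm births 29 to 34 weeks; term births uniform from 37 to 41.5 weeks (mean 39.25); alpha 0.025 per side.

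**The plan's own figure.** n = 2p(1−p)(z₀.₉₇₅ + z₀.₉₅)²/0.20² = 0.5 × (1.960 + 1.645)²/0.04 = 162.4 per arm, or 172.3 with continuity correction. The stated 170 per arm is reproduced closely; uncorrected power at 170 is 91.6%.

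**Women undelivered at a stop.** In steady accrual this is 3.45 × mean weeks from randomisation to delivery, where the mean interval = (mean preterm gestation + 39.25)/2 − mean entry gestation. For entry at 14 to 24 weeks and mean preterm gestation 32.4, it is (32.4 + 39.25)/2 − 19 = 16.8 weeks, and 3.45 × 16.8 = 58.

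**Naive preterm rate at month T, outcomes captured at delivery.** Rate = (T − m_p)/[(T − m_p) + (T − m_t)], where m_p and m_t are the mean months from randomisation to a preterm and a term birth. For the same set, m_p = 13.4/4.348 = 3.082 and m_t = 20.25/4.348 = 4.657. At month 12 this gives 8.918/(8.918 + 7.343) = 54.8%.

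| Entry (weeks) | Mean preterm gestation | Undelivered: formula / simulated | Naive rate, month 12: formula / simulated | Naive rate, month 18: formula / simulated |
|---|---|---|---|---|
| 14-24 | 32.4 | 58 / 58 | 54.8% / 54.7% | 52.8% / 53.1% |
| 14-24 | 29.0 | 52 / 52 | 56.9% / 56.8% | 54.1% / 53.8% |
| 20-24 | 34.4 | 51 / 51 | 53.2% / 53.1% | 51.9% / 51.9% |
| 16-24 | 32.5 | 55 / 55 | 54.6% / 54.6% | 52.7% / 52.6% |

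Over the wider set of assumptions tried, 45 to 61 women are undelivered, which corresponds to a mean interval of 13.0 to 17.7 weeks. As shares this is 45/180 = 25% to 61/180 = 34% at month 12, and 45/270 = 17% to 61/270 = 23% at month 18. To fall to 30 women, the mean interval would have to be 30/3.45 = 8.7 weeks. The naive excess is about 3.5 to 6 points at month 12 and 2 to 3.5 at month 18; the most extreme timing sets stretch this to roughly 3 to 7 and 2 to 4.

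**Outcomes captured only after neonatal discharge** (assumed at about 38 weeks postmenstrual age). In the first three sets the simulated naive rate is 50.8-51.3% at month 12 and 50.6-50.8% at month 18. About 7 to 16 further women, delivered but not yet discharged, then also lack an outcome.

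**Power.** Pairwise equivalence power = 2Φ(0.20/SE − 1.96) − 1, with SE = √(0.5/n per arm).

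- Month 18, 270 randomised: n = 90, SE = 0.0745, power 53%. With 56 lost: n = 71.3, SE = 0.0837, power 33%.
- Month 24, 360 randomised: 75% with all outcomes, 63% with 56 lost.

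**The case against.** - **Different scopes.** A reader might infer that sections 3.7 and 8.2.4 flatly contradict each other. They do not: one governs a woman's own withdrawal, the other the end of the whole trial. Section 3.7 is also conditional. Consent is sought for delivery details, the outcome may be refused, and nothing more is collected from a woman who loses capacity. What stands is a tension: a woman who withdraws from a running trial may be followed more fully than one who stays in a stopped trial. Section 8.2.1 likewise describes a running trial, though its window is cut short when follow-up matters most.
- **Size of the rate distortion.** Section 6 says "The primary and secondary outcome data will be collected after discharge from neonatal care". Preterm infants usually stay longer, which offsets their earlier birth and leaves about 1 point or less. This stands, so the 3.5 to 6 points cannot be given as the expected size. More women then have no outcome.
- **No shown effect on the comparison.** A reader might infer a biased treatment effect. The excess raises the rate in all arms, while section 5 reports odds ratios and risk differences between arms. Restricting to women who would have reached 37+0 by the stop recovers 50% in the simulation, if their outcomes were collected. The lost women are not recovered.
- **Not literally every woman.** About 4 of those still pregnant are already past 37+0, so their status on the primary endpoint can be inferred.
- **Contingent and already weak.** The rule bites only on an early stop, and such a trial has low power in any case (53% at month 18 with every outcome kept). The allowance of 30 was set for a completed trial, so it is a yardstick rather than a limit that is breached. This lowers the priority but does not justify discarding outcomes. The protocol does provide for stopping on safety or efficacy (section 7.13) and for review at least annually (section 7.14).

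**Conclusion.** The point holds as a defect in the stopping clause. Followed literally, section 8.2.4 costs the primary outcome and safety follow-up of about 45 to 61 women at any stop during recruitment, less the few already past 37+0. At month 18 the loss takes equivalence power from 53% to about 33%. These counts rest on 15 women per month, 50% preterm birth and assumed entry and delivery timing; the conclusion survives all the timing assumptions tried.

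The main harm is lost outcomes, precision and safety data. An inflated crude preterm rate is possible, but its size depends on when outcomes are captured. The documents do not support a claim of bias between arms. Because the rule matters only if the trial stops early, this is something that should be fixed, not a critical flaw.

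**What to change.** Replace the sentence in section 8.2.4 with wording to this effect: on premature discontinuation, delivery, neonatal and safety outcomes of all randomised women continue to be collected from records to the planned end of follow-up and are included in the analysis, unless a woman refuses. Reconcile section 8.2.4 with sections 3.7 (Withdrawal from study) and 8.2.1, so that a trial-level stop, an individual withdrawal and the safety window follow one stated rule. The change concerns data collection only.

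The cost is one sentence in an amendment and a few months of note review after any stop. It also needs a check that the consent form covers record access after termination; section 7.3 mentions only inspection of records by regulatory authorities, and the form itself was not available here. The amendment should be made before any stop, because afterwards further collection would depart from the protocol.

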## 9 Protocol amendments

Any changes in research activity, except those necessary to remove an apparent, immediate hazard to the participant, must be reviewed and approved by the Chief Investigator and the Co-Sponsors notified. Substantial amendments to the protocol must be submitted in writing to the appropriate REC, Regulatory Authority and local R&D for approval prior to participants being enrolled into an amended protocol.

## 10 Protocol violations and deviations

The Investigator should not implement any deviation from the protocol except where necessary to eliminate an immediate hazard to trial participants. In the event that an Investigator deviate deviation from the protocol, the nature of and reasons for the deviation should be recorded in the electronic clinical research files. If this necessitates a subsequent protocol amendment, this will be submitted to the REC, Regulatory Authority and local R&D for review and approval by the Chief Investigator.

[figure not shown]

## 11 Direct Access to Source Data and Documents

Meetings will be held on a regular basis by the research team to monitor and audit the conduct of the research and review aspects of the SuPPoRT study's progress. The Investigator(s) will permit trial-related monitoring, audits, REC review, and regulatory inspections by providing the Sponsor(s), Regulators and REC direct access to source data and other documents (e.g. patients' case sheets, blood test reports, X-ray reports, histology reports etc).

## 12 Quality Assurances

Monitoring of this trial will be to ensure compliance with Good Clinical Practice and scientific integrity will be managed and oversight retained, by the KHP-CTO Quality Team.

## 13. Data handling

The Chief Investigator will act as custodian for the trial data. Patient data will be anonymised. All anonymised data will be stored on a password protected computer. All trial data will be stored in line with the Medicines for Human Use (Clinical Trials) Amended Regulations 2006 and the Data Protection Act and archived in line with the Medicines for Human Use (Clinical Trials) Amended Regulations 2006 as defined in the Kings Health Partners Clinical Trials Office Archiving SOP.

## 14 Insurance / Indemnity

The Co sponsor's King's College London and Guy's and St Thomas NHS Foundation Trust will provide insurance and indemnity.

## 15 Financial Aspects

Funding to conduct the trial is provided by Tommy's Charity and the National Institute for Health Research (NIHR).

## 16 Publication Policy

It is intended that the results of the study will be reported and disseminated at international conferences and in peer-reviewed scientific journals

## 17 End of the study

The end of study declaration will be submitted to the relevant authorities following 28 days or discharge from hospital (whichever soonest) of the last woman recruited to the project. The end of the study will be reported to the REC and Regulatory Authority within 90 days, or 15 days if the study is terminated prematurely.

The Investigators have the right at any time to terminate the study for clinical or administrative reasons.

Signature

Chief Investigator

15/03/18

Date

[figure not shown]

### Schedule of Visits

| Procedure                                                             | Screening & randomisation
14 +0 -23 +6 weeks gestation | Intervention (day 0)
14 +0 -23 +6 weeks gestation | Baseline visit (day)
1-4 weeks after procedure | Follow up visits (if clinically indicated) | Final visit
34 +0 -38 +6 weeks' gestation | Note review (no visit required)              |
|-----------------------------------------------------------------------|---------------------------------------------------------------------------------|----------------------------------------------------------------------------|---------------------------------------------------|--------------------------------------------|--------------------------------------------------------------------|----------------------------------------------|
| Visit window (± days)                                                 | -7 to 0 days                                                                    | Day 0                                                                      | 7-28 days                                         | Approximately 2-4 weekly                   | 3                                                                  | Discharge from Hospital or 28 days postnatal |
| Informed consent                                                      | C                                                                               |                                                                            |                                                   |                                            |                                                                    |                                              |
| Medical history and concomitant medications                           | C                                                                               |                                                                            | C                                                 | O                                          | C                                                                  |                                              |
| Transvaginal ultrasound Scan                                          | C                                                                               |                                                                            | C                                                 | O                                          |                                                                    |                                              |
| Biological sample collection                                          | O                                                                               |                                                                            | O                                                 | O                                          |                                                                    |                                              |
| Adverse events (AEs) and changes to interventions                     |                                                                                 |                                                                            | C                                                 | O                                          | C                                                                  | C                                            |
| Count un-used medication if appropriate                               |                                                                                 |                                                                            |                                                   |                                            | C                                                                  |                                              |
| Pessary/Cerclage removal booked/performed at 37 weeks' if appropriate |                                                                                 |                                                                            |                                                   |                                            | C                                                                  |                                              |

